#### Health Care Provider Level

Team-based care is critical for optimal oncology care delivery [61,62]. Formalized communication channels, collective learning, and clear team roles are the cornerstone of collaborative care teams [63,64]. The ARROW Provider Network will use a tailored Project Extension for Community Healthcare Outcomes approach to link pediatric and adult health care providers who specialize in HIV care in the primary care facilities with counterparts at the Cancer Diseases Hospital to enable peer-to-peer learning, review of patient cases, and expert consultations [44].

Guidance documents and brochures will be created for health care providers by inviting a mix of pediatric and adult care providers to cocreating workshops. These materials will contain background information, AYA-friendly care delivery, age-appropriate engagement with AYA living with HIV, monitoring of ART adherence, flowcharts with referral pathways for early diagnosis, process steps to implement guideline-recommended cancer treatment for AYA living with HIV, documentation of services provided (eg, in the SmartCare electronic health record, which is used in HIV facilities and capture visit details, medications, and laboratory tests), and a charter with roles and responsibilities for clinical teams in the HIV treatment centers and those at the Cancer Diseases Hospital. Facilitators will use the NCCN sub-Saharan African harmonized guidelines for each cancer, along with the AYA guidelines, and create guidance documents focused on AYA living with HIV that are tailored to the Zambian setting.

Health care providers will also receive in-person training at each of the 9 HIV facilities selected to implement the ARROW program and at the Cancer Diseases Hospital before initiating the implementation trial. These training programs will also include sessions on understanding stigma faced by AYA living with HIV, delivering age-appropriate and AYA-friendly care, and best practices for communication with this population using previous training tools [17]. All HIV care providers (both pediatric and adult) will be encouraged to attend a session. We will hold additional training as needed, including refresher training sessions during the 36-month trial.

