##### Early Detection Cohort

We propose a cluster randomized study to be implemented at 18 HIV treatment facilities in Lusaka province. Three facilities serving each type of regional population (urban, periurban, or rural populations) will be randomly assigned to a study arm: the ARROW program or one-time education. Overall, 9 (50%) facilities will be assigned to each arm of the trial, with data collection at baseline and at 12-, 24-, and 36-month follow-up. At each of the 18 clinics, we will enroll 100 men and 100 females resulting in a total of 3600 participants in the early detection cohort. The 200 AYA living with HIV per facility will be selected by first reviewing the HIV register and identifying those who meet the study inclusion criteria: 15 to 39 years of age, on ART for at least 6 months, not pregnant, and with no pending plans to move from the current residence during the 3-year study duration. For all the 3600 participants, we will collect baseline data and capture information on study end points from the SmartCare system, and the supplemental data will be collected by PCs and trained study data collectors (eg, tracking referrals for all participants and obtaining results of biopsies).

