**Data elements for primary, secondary, and tertiary end points: HIV and cancer care continuum**				
	Proportion of participants completing physical examination (KS^a^ and NHL^b^) and up to date with CC^c^ screening	Confirmation of services will be based on clinical records and PC^d^ tracking tool (primary end point at 24 mo)	Biological, imaging, and clinical procedures identified through clinical records and study database	12, 24, and 36 mo
	Proportion of participants completing diagnostic tests and initiating treatment in ≤90 d	Measured as days from referral for testing and cancer diagnosis, respectively; based on chart review and study data	Biological, imaging, and clinical procedures identified through clinical records and study database	24 and 36 mo
	Proportion of participants completing repeat examinations and screening at the recommended interval	Screening every 2 y for CC and annual examination (especially when CD4^e^<100) based on the Zambian guidelines	Biological, imaging, and clinical procedures identified through clinical records and study database	36 mo
	Proportion of participants with early-stage diagnosis^f^	Stage 1 or 2 for NHL and CC; good risk for KS^g^	Biological, imaging, and clinical procedures identified through clinical records and study database	36 mo
	Proportion of participants adherent to cancer treatment^f^	Complete cancer treatment modalities as recommended	Biological, imaging, and clinical procedures identified through clinical records and study database	12 mo after diagnosis
	Proportion of participants alive at 12 mo after diagnosis^f^	Follow-up conducted by PCs and entered in study database	Biological, imaging, and clinical procedures identified through clinical records and study database	12 mo after diagnosis
	Proportion of participants with recurrent disease^f^	AYA^h^ living with HIV and cancer who experience cancer recurrence	Biological, imaging, and clinical procedures identified through clinical records and study database	36 mo
	Proportion of participants adherent to ART^i^ and viral load	Prescription filled every 3 to 6 mo; blood test	Biological, imaging, and clinical procedures identified through clinical records and study database	Annually

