**HIV status, demographics, mediating outcomes, intervention dose, and clinical services**				
	HIV status and diagnosis date	Perinatally or behaviorally infected; CD4 count	Clinic record	Baseline
	Demographics and socioeconomic status	Research Triangle Institute AYA Zambia survey	Self-report	Baseline
	Self-efficacy (AYA living with HIV)	Generalized self-efficacy Scale [69]	Self-report	Baseline and 12, 24, and 36 mo
	Social support and mental health (AYA living with HIV)	Brief social support and patient health questionnaires [69,70]	Self-report	Baseline and 12, 24, and 36 mo
	HIV and cancer stigma (AYA living with HIV)	Anticipated stigma measures [71,72]	Self-report	Baseline and 12, 24, and 36 mo
	Cancer risk (AYA living with HIV)	Updated Research Triangle Institute cancer survey	Self-report	Baseline and 12, 24, and 36 mo
	Group education and sessions (AYA living with HIV)	Number and proportion of education sessions attended (dose)	PC tool; study database	12, 24, and 36 mo
	One-on-one education (AYA living with HIV)	Number of women receiving each level of strategy (dose)	PC tool; study database	12, 24, and 36 mo
	HIV and cancer team training (health care provider)	Proportion who attended initial training sessions (dose)	PC tool; study database	12, 24, and 36 mo
	Network meetings (health care provider)	Number and proportion of meetings attended (dose)	PC tool; study database	12, 24, and 36 mo
	Clinical team knowledge, confidence in ability, and collaboration (health care providers)	Survey on skills and patient communication; stigma related to AYA living with HIV (modified Nyblade instrument [73]) and peer learning and coordination	Self-report	Baseline and annually
	Diagnostic procedures by cancer type	Number of supplemental and diagnostic tests conducted	Clinical record	12, 24, and 36 mo
	Treatment modality by cancer type	Chemotherapy sessions; surgery; type of radiation	Clinical record	12, 24, and 36 mo

^a^KS: Kaposi sarcoma.

^b^NHL: non-Hodgkin lymphoma.

^c^CC: cervical cancer.

^d^PC: peer counselor.

^e^CD4: cluster of differentiation 4.

^f^Among AYA living with HIV and diagnosed with cancer.

^g^NHL stage based on the Lugano classification, CC stage based on the International Federation of Gynecology and Obstetrics, and KS stage based on the AIDS Clinical Trial Group system.

^h^AYA: adolescents and young adults.

^i^ART: antiretroviral therapy.

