### Analysis of Hypotheses

We will use an intent-to-treat approach to test the hypotheses (related to the dual primary and secondary end points) that AYA living HIV in the ARROW program, compared with those receiving one-time education, will have higher uptake of early diagnostic services, increased adherence to treatment, and improved outcomes.

For the facilities assigned to the intervention group in the early detection cohort, we will examine the effects at the individual level across the 2 randomization groups. Given the need to consider the influence of the cluster randomization, we will use generalized estimating equation models to estimate the effect across the trial arms. If the Hausman assumption of correlation between the random and fixed effects is violated, then we will include fixed effects representing cluster identification [74]. For the cancer treatment cohort, we will generate summary statistics for the end points and test statistical significance. We will also conduct logistic regressions to identify key factors that predict adherence.

For both trials, we will adjust for baseline covariates, including sociodemographic factors, should the initial descriptive analyses suggest differences in the distribution of these factors across the study arms. We will also explore the use of propensity scores to control for systematic differences between the AYA living with HIV in the 2 trial arms. In further analyses, we will compare differences in mediating outcomes across the randomized groups and examine the potential moderating roles of key individual behavioral and social factors hypothesized to influence adherence along the cancer care continuum (eg, social support, stigma, and self-efficacy), as shown in Figure 1. We will test the “dose” of the ARROW program received as a covariate in these models. In additional analysis, we will explore differences in the end points by age groups and type of cancer, as appropriate. We will also assess whether knowledge, self-efficacy, social support, and stigma differ by age groups and among AYA living HIV, both with and without cancer.

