For measures where we have baseline and 12-, 24-, and 36-month data (eg, self-efficacy and stigma), we will perform difference-in-difference analysis, which will allow for comparisons over time and across the study arms. To understand potential variation across the HIV treatment facilities, we will conduct comparisons to analyze differences in mediating outcomes for the AYA living with HIV and the study end points. Furthermore, to understand ARROW program’s impact on health care providers, we will assess dose of the intervention (network session attendance) and change in knowledge, confidence in ability to care for AYA living with HIV, and peer collaboration.

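### Table 2 schedules no baseline reading of examination or cervical screening, and adjustment for prior uptake is not prespecified, which forgoes precision with only 9 facilities per arm

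*Protocol article*

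**What the plan says.** Data Collection presents Table 2 as the schedule of what is collected at baseline and at the three annual follow-ups. In the row for completed KS/NHL examination and up-to-date cervical screening, the specification reads "Confirmation of services will be based on clinical records" and then adds the peer counselor tracking tool. The timing entry is 12, 24 and 36 months. By contrast, self-efficacy, social support and mental health, stigma and cancer risk carry the entry "Baseline and 12, 24, and 36 mo". The cancer risk instrument is the self-reported "Updated Research Triangle Institute cancer survey", whose items are not shown.

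Under Analysis of Hypotheses, for the cluster trial, "we will use generalized estimating equation models to estimate the effect across the trial arms". Baseline covariates, with sociodemographic factors given as an example, enter only if the initial descriptive analyses suggest a difference between arms. Difference-in-difference analysis is reserved for measures with a baseline value, and the examples given are self-efficacy and stigma.

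On data sources, the design section for the early detection cohort says that for all participants "we will collect baseline data and capture information on study end points from the SmartCare system". The Health Care Provider Level section describes SmartCare as a record "which is used in HIV facilities and capture visit details, medications, and laboratory tests". The limitations section accepts that cluster randomization raises the risk of baseline differences, and proposes to examine them from the HIV registers and to use propensity score weights.

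**The concern.** With 18 facilities, the standard error of the arm comparison comes mostly from variation between facilities. A facility that already examined and screened more of its patients is likely to do so again at 12 months, whatever its arm. Prior uptake of the same service is therefore a natural covariate, yet it has no scheduled baseline reading and is not named in the analysis.

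The stated adjustment rule does not fill this gap. A covariate earns its place by predicting the outcome, and not by happening to differ between arms. A rule triggered by the data also leaves the primary model open until the data have been seen. On the Table 2 schedule, prior examination and screening would not be among the variables inspected.

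Cervical screening makes the matter sharper. Table 2 gives a two-year screening interval. If being up to date follows that interval, status at 12 months looks back as far as 12 months before enrolment. A woman screened in that stretch counts as a success in either arm regardless of the programme.

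**Working it through.** **Inputs from Sample Size and Recruitment and the design section.** 9 facilities per arm; 200 participants per facility, of whom 100 are women; 10% attrition, leaving m = 180 (examination) or 90 (screening); ICC 0.03 to 0.05; two-sided α = 0.025 per end point; 15% versus 35% (examination) and 20% versus 40% (screening).

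**1. The plan's own power, without baseline adjustment.** Effective n per arm = 9m / [1 + (m − 1) × ICC]. At ICC 0.05:
- Examination: 1620 / 9.95 = 162.8. SE = √[(0.15×0.85 + 0.35×0.65) / 162.8] = √(0.355 / 162.8) = 0.0467.
- Screening: 810 / 5.45 = 148.6. SE = √[(0.20×0.80 + 0.40×0.60) / 148.6] = √(0.40 / 148.6) = 0.0519.

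Normal-approximation power is 97.6% (examination) and 94.0% (screening). With t on 16 df it is 95.5% and 90.4%. At ICC 0.03 all figures are higher. The stated claims of over 90% and over 85% are reproduced.

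**2. Chance imbalance in prior uptake.** Assume a prior rate of 20%, and ignore the urban, periurban and rural strata, which may reduce these figures.
- Between-facility SD = √(ICC × 0.2 × 0.8) = 6.9 points at ICC 0.03 and 8.9 points at 0.05.
- SD of the arm difference = that × √(2/9) = 3.3 and 4.2 points. A difference larger than one SD arises by chance about one time in three.
- Adding sampling error for 100 women per facility, √[2 × 0.16 × (ICC + (1 − ICC)/100) / 9] = 3.8 and 4.6 points. The chance of a gap above 5 points is then 18% to 28%.

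**3. Gain from adjustment.** Let r be the correlation between a facility's prior and 12-month rates. The documents do not give r, so a range is assumed. Variance per facility is proportional to ICC × (1 − r²) + (1 − ICC)/m. At ICC 0.05:

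| r | SE, examination | SE, screening | Power (t, 15 df), examination | Power (t, 15 df), screening |
|---|---|---|---|---|
| none | 0.0467 | 0.0519 | 95.5% (16 df) | 90.4% (16 df) |
| 0.3 | 0.0448 | 0.0499 | 96.7% | 92.2% |
| 0.5 | 0.0411 | 0.0462 | 98.6% | 95.6% |
| 0.7 | 0.0348 | 0.0400 | 99.9% | 99.0% |

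The SE falls by 4% to 25% for examination and by 4% to 23% for screening. Any gain from the participant's own prior status is not counted.

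**The case against.** Covariate choice is usually left to the analysis plan, which is not shown, and a journal article condenses. That stands as far as silence goes. But the article does state an adjustment rule and an explicit timing column, and the point concerns those.

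A reader might infer that the primary comparison cannot be adjusted for prior uptake. The text does not support that. Baseline data are collected on everyone, the covariate list is open, propensity scores are contemplated, registers are used to look at baseline differences, and the baseline cancer survey may hold screening items (by self-report, whereas the end point rests on records and the tracking tool). For cervical screening, a two-year interval would itself require reading some pre-enrolment records.

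A reader might also infer that SmartCare already holds the needed history. The article says only that it captures visits, medications and laboratory tests, and it lists documentation of services as content of new provider guidance. Eligibility needs just 6 months on ART, so a longer look-back is not assured. Peer counselors conduct KS/NHL examinations in the ARROW arm and their tool helps confirm the end point, so a baseline from records alone may not measure quite the same thing. This could lower r.

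Nor does any section say that prior uptake is the strongest predictor. At r = 0.3 the gain is only 4%.

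Finally, the 4.2-point imbalance is already part of the clustered standard error. It must not be counted twice or called bias. All of these points stand; they limit the claim without removing it.

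**Conclusion.** The point holds as a recommendation on precision and chance imbalance. Table 2 schedules no baseline reading for the two services in the first primary end point, prior status is not named as a covariate, and the only stated adjustment depends on observed arm differences. Prespecified adjustment for the baseline outcome is better than that rule.

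Its size depends on two things: the plan's ICC of 0.03 to 0.05, which gives a chance arm difference with an SD of about 3.3 to 4.2 points at 20% uptake before sampling error and stratification; and an assumed r of 0.3 to 0.7, which gives a 4% to 25% smaller standard error at ICC 0.05. It would be wrong to conclude that the trial is underpowered or its primary estimate biased: stated power is met as planned, and the GEE model is chosen to account for clustering.

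**What to change.** - Add a baseline row to Table 2 for KS/NHL examination and cervical screening status, extracted from clinical records (SmartCare where recorded) in both arms.
- End the look-back window before ARROW launch and use the same calendar dates in both arms. The Results section reports that ARROW was live at all intervention facilities by December 2024, while recruitment ran to February 2025. A window closing at each person's enrolment could therefore take in services the programme itself produced.
- Prespecify the facility's baseline proportion and the participant's own baseline status as covariates in the primary model for the matching end point, whether or not the arms look different.
- Before committing, check how completely each service was recorded before the trial, especially KS/NHL examinations, and whether this was similar in the two arms.

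The cost is one retrospective extraction, still possible with recruitment closed because the records predate launch, and one cluster-level degree of freedom per model. Incomplete pre-trial recording would reduce the gain.

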## Introduction

### Background

Adolescents and young adults (AYA), those aged 15 to 39 years, represent a growing share of people living with HIV worldwide. Zambia has one of the highest prevalence rates of HIV among AYA in sub-Saharan Africa; as of 2023, there are approximately 90,000 AYA between the ages of 10 and 19 years living with HIV, with only half of that population receiving antiretroviral therapy (ART) [1]. The AYA population also accounts for half of all new recorded infections in the country [1]. Compared to their peers who are living without HIV, AYA living with HIV are at an increased risk of developing cancer [2-4]. Cancers most frequently diagnosed among AYA living with HIV in Zambia are Kaposi sarcoma (KS), non-Hodgkin lymphoma (NHL), and cervical cancer (CC) [5-9]. The incidence of these cancers increases with a lower cluster of differentiation 4 cell count (CD4); therefore, adherence to ART is paramount [10]. Unfortunately, AYA living with HIV are among the most vulnerable groups with poor adherence to ART, and there is no large-scale cancer control program to facilitate early diagnosis and completion of guideline-recommended treatments in Zambia [11,12].

A cancer program focused on AYA living with HIV and tailored to the Zambian limited resource setting is needed to reduce premature mortality. Data on malignancies within this group are sparse, but late-stage presentation, unplanned breaks from cancer treatment, and abandonment of treatment have been reported among young patients with cancer in resource-limited settings [13-15]. These factors result in high morbidity and premature mortality among AYA living with HIV and diagnosed with cancer. Late-stage presentation and lack of treatment adherence are key drivers of premature cancer mortality among AYA living with HIV in Zambia.

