##### Cancer Treatment Cohort

The primary end point is the proportion of those who are adherent to cancer treatment (complete all treatment modalities as prescribed; 2-week delays will be allowed) at 12 months after diagnosis, the secondary end point is the proportion alive at 12 months after diagnosis, and the tertiary end point is the proportion with recurrence at 24 and 36 months (among those with 24- and 36-month follow-up).

For all the AYA living with HIV, we will report adherence to ART (proportion of those filling prescriptions at least every 3 to 6 months) and viral load at 12, 24, and 36 months. Viral load testing is generally conducted at least annually for AYA living with HIV as part of routine guideline-recommended practice. We will reinforce the need for regular viral load testing as part of health care provider training and have set aside funds to conduct viral load testing for study participants for whom this information is unavailable in the medical record.

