##### Cancer Treatment Cohort

We will use stratified random assignments to place patients in each arm of the trial. Once we have enrolled 10 patients with each type of cancer, we will randomly assign half to the ARROW program and the other half to the one-time education arm. All patients will have a minimum of 12 months of follow-up, and some will have up to 36 months of follow-up. Data will be collected at baseline and then annually for the 3-year duration of the trial from the AYA living with HIV through surveys and by abstracting information from the Cancer Diseases Hospital records. The sample size (n=500) was calculated using conventional specifications (α=.05; 2-sided tests) based on the primary end point and allowing for an absolute 15% point improvement; the estimated current level of adherence is 75%, which will increase to at least 90% with the ARROW program. With 50% (250/500) of the patients in each arm, we will have more than 90% power to detect this difference.

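### Cancer treatment cohort: the 12-month survival comparison is planned unadjusted, with no named role for stage at diagnosis, and so gives up some precision that could be recovered cheaply

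*Protocol article*

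**What the plan says.** All references are to the protocol article.

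- **Prognosis.** The Background states: "Late-stage presentation and lack of treatment adherence are key drivers of premature cancer mortality among AYA living with HIV in Zambia". The section on cost-effectiveness also uses mortality by stage in its projections.
- **Assignment.** Patients enter the cancer treatment cohort already diagnosed. Under Sample Size and Recruitment: "Once we have enrolled 10 patients with each type of cancer, we will randomly assign half to the ARROW program", with the other half going to one-time education. Cancer type is the only stratification factor named.
- **End points.** Adherence at 12 months is primary, and "the secondary end point is the proportion alive at 12 months after diagnosis". The stated power is for adherence: "the estimated current level of adherence is 75%, which will increase to at least 90% with the ARROW program" and "With 50% (250/500) of the patients in each arm, we will have more than 90% power to detect this difference". No survival rates or survival power are given.
- **Stage.** Table 2 has one stage row, defined as "Stage 1 or 2 for NHL and CC; good risk for KS" and timed at 36 months. A footnote names the staging system for each cancer. The baseline rows cover HIV status, CD4 count, demographics and psychosocial scales.
- **Analysis.** Analysis of Hypotheses plans summary statistics and a significance test for this cohort, and logistic regressions for predictors of adherence. For both trials, "we will adjust for baseline covariates, including sociodemographic factors, should the initial descriptive analyses suggest differences" between arms. Subgroups by age and cancer type are mentioned. Stage is not.

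**The concern.** Stage at diagnosis is fixed before a hospital patient is assigned, so it is a legitimate baseline covariate. The document itself treats it as strongly related to death. The stated method does not use it: the main comparison is unadjusted, and adjustment depends on what a descriptive comparison of the arms happens to show.

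Covariate adjustment earns its keep by removing outcome variance that a prognostic factor explains, whether or not the arms look balanced. An imbalance trigger therefore misses most of the benefit, and it leaves the choice of model to be made after data have been seen. At stake is the precision of the 12-month survival comparison, for which no power is claimed and where efficiency matters more than it does for adherence.

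**Working it through.** **1. The plan's own figure.** Inputs from Sample Size and Recruitment: 250 per arm, 75% v 90% adherence, two-sided alpha 0.05.

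Power = Φ{[d − 1.96·√(2p̄(1−p̄)/n)] / √([p1(1−p1)+p2(1−p2)]/n)}

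With d = 0.15, p̄ = 0.825 and n = 250: (0.15 − 1.96×0.03399)/0.03332 = 2.50, so power is 99.4%. This agrees with the claim of more than 90%.

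**2. Variance explained by stage.** Let q be the late-stage share, pE and pL the outcome rates in early and late stage, and m the overall rate.

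R² = q(1−q)(pE−pL)² / [m(1−m)]; effective N = 500/(1−R²); SE ratio = √(1−R²)

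The documents give neither q nor survival by stage. Both are assumed here, with q = 0.6.

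| Assumed 12-month survival, early / late | m | R² | SE ratio | Effective N |
|---|---|---|---|---|
| 90% / 80% | 0.84 | 0.018 | 0.991 | 509 |
| 85% / 65% | 0.73 | 0.049 | 0.975 | 526 |
| 90% / 70% | 0.78 | 0.056 | 0.972 | 530 |
| 90% / 60% | 0.72 | 0.107 | 0.945 | 560 |
| 90% / 50% | 0.66 | 0.171 | 0.910 | 603 |
| 95% / 50% | 0.68 | 0.223 | 0.881 | 644 |

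The stage mix matters less than the gap: at 90% / 50%, R² is 0.190 with 50% late stage and 0.143 with 70%.

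**3. Power for a 10-point survival gain**, using n = 250 unadjusted and 250/(1−R²) adjusted in the formula of step 1:

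| Early / late | Unadjusted | Adjusted | Gain |
|---|---|---|---|
| 90% / 70% | 84.7% | 86.7% | 2.0 points |
| 90% / 60% | 75.9% | 80.4% | 4.5 points |
| 95% / 50% | 71.3% | 81.7% | 10.4 points |

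**4. Check by simulation** (40,000 runs, 250 per arm, crude v stage-standardised risk difference). The variance ratio was 1.05, 1.10 and 1.22 for the three scenarios of step 3. The formula gives 1/(1−R²) = 1.06, 1.12 and 1.29. The formula is slightly generous, because it uses control-arm rates for both arms while the simulated benefit narrows the stage gap in the ARROW arm. A separate simulation (6,000 runs, 40% early stage, log-odds effect 0.5) gave power of 61.4% to 63.0% (85% / 65%), 58.3% to 62.6% (90% / 60%) and 58.7% to 66.3% (90% / 50%). Rejection under the null was 4.8% to 5.6%.

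**5. Adherence.** Assumed early / late rates of 81% / 71% give R² = 0.013 and effective N 506. Rates of 87% / 67% give R² = 0.051 and effective N 527. Power goes from 99.4% to at most about 99.6%.

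**6. Chance imbalance.** The 95% range for the difference in late-stage share between arms is 1.96·√(2×0.6×0.4/250) = 8.6 points. At a 40-point survival gap this moves the crude survival difference by 0.086×40 = 3.4 points. At a 30-point gap it moves it by 2.6 points. For comparison, the unadjusted 95% half-width at 66% survival is 1.96·√(2×0.66×0.34/250) = 8.3 points.

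**The case against.** The strongest reply is that this is a condensed article. A covariate list is normally left to the analysis plan, the list here is open, and stage is not excluded. That is fair as far as the missing name goes. It does not remove the point, because the article does state a method (an unadjusted test, with adjustment only on apparent imbalance), and a better one is available at little cost.

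Four stronger readings are tempting, and the documents do not support them:

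- **Stage is not collected for these patients.** Table 2 is not a complete baseline list. It also has no baseline row for cancer type or date of cancer diagnosis, yet assignment and the 12-month end points require both. The 36-month stage row matches the secondary end point of the early detection cohort. Hospital records are abstracted, so stage may well be available. It follows that the imbalance check cannot be said to be blind to stage.
- **The comparison is biased.** Under randomisation, chance imbalance in stage is sampling error that the unadjusted test already allows for. The simulated type I error is near 5%.
- **The primary end point suffers.** The Background links stage to mortality and lists poor adherence as a separate driver. Step 5 shows almost nothing to gain.
- **Assignment should have been stratified by stage.** Adjustment in the analysis recovers the precision without this.

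It also stands that cancer type, already balanced by design, may carry part of the same prognostic information. The gain beyond cancer type could therefore be smaller than the figures above.

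**Conclusion.** The point holds as one of efficiency for a secondary end point, not of validity. The planned unadjusted survival comparison is sound but gives up precision that a named, pre-assignment covariate would recover. Under assumed survival gaps by stage of 10 to 45 points, stage explains about 2% to 22% of outcome variance, equal to about 10 to 144 patients on 500. For gaps of 20 points or more, that is about 2 to 10 power points for a 10-point survival gain. The upper end needs a very strong stage effect, and simulation puts the gains a little lower than the formula. All of this rests on assumed stage mix and survival by stage, since the documents give neither. For adherence the gain is negligible.

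**What to change.** 1. Abstract stage at diagnosis for every patient in the cancer treatment cohort from the hospital records, using the Table 2 definitions, dated before assignment, with an 'unknown' category. By March 2025, 105 of 500 patients were enrolled. Their stage can be taken from existing records under the same date rule.
2. Pre-specify, before outcomes are examined, that the 12-month survival comparison adjusts for early/late stage and cancer type whether or not the arms look different. One option is logistic regression standardised to a risk difference. Keep the unadjusted difference as a sensitivity analysis.
3. The same adjustment may be used for adherence, for consistency only.

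Leave the assignment strata alone. Counted over the nine months from July 2024, 105 patients is about 12 a month. At the 20% target for NHL that is about 2.3 a month, so a batch of 10 NHL patients already takes about four months to fill. Splitting it by stage would lengthen that further.

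The cost is one abstracted field and one sentence of analysis text. The small downside is that some patients will have unknown stage.
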